**Methods/design:**

The HIGHLOW study is a multicenter randomized controlled trial in which patients are randomly assigned to high or low inferior mesenteric artery ligation during laparoscopic anterior rectal resection with total mesorectal excision for rectal cancer. Inclusion criteria are middle or low rectal cancer (0 to 12 cm from the anal verge), an American Society of Anesthesiologists score of I, II, or III, and a body mass index lower than 30. The primary end-point measure is the incidence of post-operative genito-urinary dysfunction. The secondary end-point measure is the incidence of anastomotic leakage in the two groups. A total of 200 patients (100 per arm) will reliably have 84.45 power in estimating a 20% difference in the incidence of genito-urinary dysfunctions. With a group size of 100 patients per arm it is possible to find a significant difference (α = 0.05, β = 0.1555). Allowing for an estimated dropout rate of 5%, the required sample size is 212 patients.

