### Primary and secondary endpoint measures

The primary end-point measure is the incidence of post-operative genito-urinary dysfunction compared with a preoperative base-line assessment in both groups. The secondary endpoint measures are the incidence of clinical or subclinical anastomotic leakage in the two groups and the oncological outcomes in both groups.

The incidence of clinical or subclinical anastomotic leaks will be determined either as the presence of a radiologically, endoscopically, or surgically proved fistula or as the presence of a subclinical leak observed by endoscopic examination 30 days after surgery in both groups.

Oncological outcomes will be assessed in terms of retrieved lymph nodes, number of positive lymph nodes on the root of the inferior mesenteric artery total number of lymph nodes of the mesorectum, and positive lymph nodes of the mesorectum, disease-free survival, overall survival, local recurrence, distant metastasis in both groups.

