### Sample size calculation

A two tail Fischer exact test applied to two cohorts of 100 patients each will have 84.45 power in estimating a 20% difference in the incidence of genitor-urinary dysfunctions. With a group size of 100 patients per arm it is possible to find a significant difference (α= 0.05, β= 0.1555).

With a drop-out estimated rate of 5%, the required sample size is 212 patients. If the number of drop-outs exceed 5%, we plan to ask the ethics committee to enroll more patients to be able to keep the power of analysis well above 80%.

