### Statistical analysis

The Primary end-point measure will be evaluated using Fisher’s exact test (one-sided). The different incidences of genitor-urinary dysfunction according to sex and the results of each questionnaire will be evaluated using the Mann–Whitney *U test* and the *t-*test. Mc Nemar’s test will be used to evaluate changes in questionnaires results overtime. Statistical analysis will be performed in accordance with the intention-to-treat principle.

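### Fisher's exact test for the primary endpoint is valid but conservative; Boschloo's exact test, with its version specified, would add a little power without extra patients.

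*Protocol article*

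**What the plan says.** The primary endpoint is binary: "The primary end-point measure is the incidence of post-operative genito-urinary dysfunction compared with a preoperative base-line assessment in both groups". For the comparison between arms, the Statistical analysis section of the protocol article says: "The Primary end-point measure will be evaluated using Fisher’s exact test (one-sided".

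The Sample size calculation section uses the same test with the other sidedness: "A two tail Fischer exact test applied to two cohorts of 100 patients each will have 84.45 power in estimating a 20% difference". It gives the error rates as "it is possible to find a significant difference (α= 0.05, β= 0.1555". The abstract repeats the figure for 100 per arm, and enrolment is inflated for attrition: "With a drop-out estimated rate of 5%, the required sample size is 212 patients".

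Event rates per arm are not given, only the size of the difference. No alpha is stated separately for the one-sided test. No unconditional exact test or mid-p correction is mentioned.

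**The concern.** Fisher's test conditions on both margins of the 2 x 2 table. Under binomial sampling in this design only the arm sizes are fixed; the total number of patients with dysfunction is random. Conditioning on that total makes the set of attainable p-values coarse, so the real type I error stays below the nominal 5%.

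Some tables that an exact 5% test could validly reject would then be reported as not significant. The protocol also commits to keeping power well above 80%, if need be by asking the ethics committee for more patients. Power available at no cost in patients bears on that aim.

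**Working it through.** **Inputs.** From the Sample size calculation: 100 per arm, alpha 0.05, a 20-point difference, power 84.45%. From the Statistical analysis section: Fisher's test, one-sided. Assumption: event rates 20% v 40%, because none are stated; other pairs are shown below.

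**Method.** Enumerate all 101 x 101 outcomes (x, y). For a rejection region R:

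- Power(p1, p2) = sum over (x, y) in R of Bin(x; 100, p1) × Bin(y; 100, p2).
- Size(p) = the same sum with p1 = p2 = p; maximum size is its largest value over p.
- Fisher: R = all tables with Fisher p ≤ α.
- Boschloo: R = all tables with Fisher p ≤ c, where c is the largest cut-off whose maximum size stays at or below α. Since c ≥ α, this region contains Fisher's region, so power cannot fall.

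**Step 1, the plan's own figures.** Two-sided Fisher at 20% v 40% gives 84.45%, an exact match (β = 1 − 0.8445 = 0.1555). The mirror pair 60% v 80% matches equally. For attrition, 100/0.95 = 105.3, rounded up to 106 per arm, gives 2 × 106 = 212.

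**Step 2, real size of Fisher's test at nominal 5%, 100 per arm.**

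| Common rate | One-sided | Two-sided |
|---|---|---|
| 5% | 2.08% | 2.09% |
| 10% | 3.10% | 2.87% |
| 20% | 3.50% | 3.29% |
| 30% | 3.69% | 3.48% |
| 40% | 3.58% | 3.63% |
| 50% (maximum) | 3.84% | 4.00% |

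Boschloo's maximum size is 4.95% one-sided and 4.96% two-sided (cut-off c = 0.0638 for the latter), so it remains a valid 5% test.

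**Step 3, power at exactly 100 v 100, α = 0.05.**

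| Rates | One-sided Fisher → Boschloo | Gain (points) | Two-sided Fisher → Boschloo | Gain (points) |
|---|---|---|---|---|
| 10% v 30% | 96.7% → 97.3% | 0.6 | 93.5% → 94.8% | 1.4 |
| 20% v 40% | 91.0% → 92.1% | 1.2 | 84.45% → 86.9% | 2.5 |
| 30% v 50% | 86.7% → 89.4% | 2.8 | 79.2% → 82.8% | 3.6 |
| 40% v 60% | 86.0% → 88.0% | 2.0 | 78.7% → 79.1% | 0.5 |

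Gains are taken from unrounded powers. At one-sided 0.025 and 20% v 40%, power again goes from 84.45% to 86.9%, with maximum size 2.0% for Fisher and 2.48% for Boschloo.

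**Step 4, unequal arms.** With a 5% attrition allowance, exact balance is unlikely. Take 98 patients at 40% and 102 at 20%. Two-sided Fisher then has size 4.2% at a common rate of 30%, maximum 4.7%, and power 87.1%. Boschloo has 88.1%, a gain of 1.0 point. With 104 v 102 the two-sided gain can be as low as 0.4 points. The one-sided 0.05 gain at 98 v 102 is 2.2 points.

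**Step 5, the version matters.** A two-sided Boschloo p-value is sometimes computed by doubling the smaller one-sided value, as SciPy does. With unequal arms that version need not contain Fisher's rejection region. For 5/102 v 13/98, Fisher's two-sided p is 0.048 and the doubled Boschloo p is 0.052. Its power at 102 v 98 is 87.5% against Fisher's 87.1%.

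**Step 6, single tables at 100 v 100.** Two-sided, 20 v 33 events: Fisher 0.054, Boschloo 0.040. One-sided, 20 v 31 events: Fisher 0.052, Boschloo 0.039.

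**The case against.** The strongest reply is that nothing is wrong here. Fisher's test controls the type I error, and the protocol computed its power for Fisher's test, so the conservatism is already paid for in the sample size. In a randomised trial, conditioning on the total event count also has its own justification: under the sharp null of no effect that total does not depend on allocation. All of this stands. It limits the point to one of efficiency but does not remove the gain.

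A reader might go further in four ways that the documents and the arithmetic do not support.

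- *Fisher's test always runs at about 3.5%.* The figure depends on the unstated common rate and on equal arms. It is about 2.1% at a rate of 5%, and 4.2% two-sided at 102 v 98 with a rate of 30%.
- *Boschloo's test saves 8 patients per arm.* It reaches 84.66% with 92 per arm, but only two-sided and with exactly equal arms. It does not justify enrolling fewer patients.
- *A result such as 20/100 v 33/100 would be lost.* That holds only for the two-sided test. Under the one-sided test actually named, Fisher's p is 0.027, already below 0.05.
- *Any Boschloo test rejects whenever Fisher's does.* This fails for the doubled two-sided version when arms are unequal.

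The mismatch between the two-tailed design and the one-sided analysis is a separate and larger problem: 90.98 − 84.45 = 6.5 points of power at nominal 0.05. It has to be resolved first.

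**Conclusion.** The point holds as a modest improvement. At 100 per arm, Fisher's test has a maximum real size of 3.8% one-sided or 4.0% two-sided against a nominal 5%. Boschloo's test with the same ordering uses more of the level and never has less power.

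At an assumed 20% v 40%, and allowing for slightly unequal arms, the expected gain is:

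- one-sided 0.05: about 1 to 2 points;
- two-sided 0.05: about 0.4 to 2.5 points, the upper end only with exactly 100 v 100;
- one-sided 0.025: about 2 to 3 points.

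The stated 84.45% is not an error, and the documents do not show the trial to be underpowered on this account. The sizes rest on the assumed event rates and independent binomial arms; the direction of the gain does not depend on the rates.

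**What to change.** 1. First settle whether the primary test is one-sided or two-sided and at which alpha, and state it identically in the Sample size calculation and Statistical analysis sections.
2. In the Statistical analysis section, name Boschloo's exact unconditional test for the primary comparison between arms. Define it with the Fisher p-value of the chosen sidedness as the ordering statistic. If the test is two-sided, say that the doubled one-sided version is not meant.
3. In the Sample size calculation, say that 84.45% is the two-sided Fisher figure at an assumed 20% v 40%. Give the power of the chosen test at the same rates: 86.9% for two-sided Boschloo or 92.1% at one-sided 0.05, each with exactly 100 v 100.
4. Keep 100 evaluable per arm and 212 enrolled, and report Fisher's test as a sensitivity analysis.

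The cost is about one sentence in each of two sections, plus a check that the software computes the version named. No patients or data are added. The Trial status section says recruitment has not opened, so the change can be made before any outcome is seen. The downside is that surgical readers know Boschloo's test less well.

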### Preoperative evaluation

Patients with a preoperative diagnosis of adenocarcinoma of the middle or lower rectum and who satisfy the inclusion criteria will be asked to participate in the HIGHLOW trial. Once informed consent is obtained, investigations will include questionnaires for the International Index of Erectile Function [27], International Consultation on Incontinence Questionnaire [28], International Prostatic Symptoms Score, Female Sexual Function Inde [29] Uroflowmetry and ultrasound measurement of post-void bladder volume will be performed pre-operatively for all patients.

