### Post-operative evaluation

Colonoscopy will be performed 30 days after surgery to evaluate anastomosis (leakage, signs of ischemia) [26]. Accurate description and pictures of the anastomosis will be produced. Questionnaires for the Internation Index of Erectile Function [27], International Consultation on Incontinence Questionnaire [28], International Prostatic Symptoms Score, and Female Sexual Function Index [29] will be administrated, and uroflowmetry and ultrasound measurement of post-void bladder volume will be performed 1 and 9 months post-operatively. Retrieved lymph nodes will be collected from the histopathological examination, and the number of positive lymph nodes on the root of the inferior mesenteric artery, the total number of lymph nodes on the mesorectum, and the number of positive lymph nodes on the mesorectum will be recorded Oncological follow up will be carried out for 5 years, according to National Comprehensive Cancer Network Guidelines [30] Version 1.2015 Rectal Cancer/Surveillance (www.nccn.org).

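### The supportive functional analyses are mis-specified: rank and t-tests are named for incidences by sex, and McNemar's test for questionnaire scores taken at three times

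*Protocol article*

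**What the plan says.** The Statistical analysis section of the protocol article has three elements that bear on function.

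- Primary endpoint: "The Primary end-point measure will be evaluated using Fisher’s exact test (one-sided").
- By sex, and by questionnaire: "The different incidences of genitor-urinary dysfunction according to sex and the results of each questionnaire will be evaluated using the Mann–Whitney" test, with a t-test named alongside.
- Over time: "Mc Nemar’s test will be used to evaluate changes in questionnaires results overtime".

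The primary endpoint itself is binary and refers to baseline: "The primary end-point measure is the incidence of post-operative genito-urinary dysfunction compared with a preoperative base-line assessment in both groups". The instruments are listed under Preoperative evaluation, beginning with "questionnaires for the International Index of Erectile Function" and continuing with an incontinence, a prostatic-symptom and a female sexual function questionnaire. Post-operative evaluation repeats them, and adds that "uroflowmetry and ultrasound measurement of post-void bladder volume will be performed 1 and 9 months post-operatively". Each functional measure therefore has three planned time points: before surgery, 1 month and 9 months.

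**The concern.** The section does more than leave detail open: it pairs named tests with named data, and two of the pairings do not fit.

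- **Incidence by sex.** This is a proportion. The Mann-Whitney and t-tests are meant for ordinal or continuous values. The same section already uses Fisher's exact test for this endpoint overall, so one endpoint would be tested by two methods that need not agree.
- **Change over time.** McNemar's test needs a yes/no result on the same patient at exactly two times. One sentence earlier the same questionnaire results are handled as scores, and there are three times. Even on a suitable binary status the test compares time points within patients. It cannot say whether high and low ligation differ, which is the aim given in the Background.
- **Scores between arms.** The two-sample tests are sound here, but as worded they make no use of the preoperative value that the plan collects.

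At stake are the readability of the by-sex and questionnaire results and some precision, chiefly for the sex-specific questionnaires, which fewer patients complete.

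**Working it through.** **1. The plan's own figures.** Inputs from Sample size calculation: two-sided Fisher test, 100 per arm, 20-point difference, α = 0.05, power 84.45%, 5% dropout, 212 patients. The two incidences are not stated. Full enumeration of two binomial arms of 100 at 40% and 20% gives two-sided Fisher power 0.8445, exactly the stated value. For dropout, 100/0.95 = 105.3, rounded up to 106 per arm, and 2 × 106 = 212. Both figures reproduce, and neither depends on the tests discussed here.

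**2. Mann-Whitney and t-test on yes/no data.** Take 35 and 22 events in two groups of 100 as an illustration. The pooled proportion is 57/200 = 0.285 and its standard error is √(0.285 × 0.715 × 2/100) = 0.0638. Then z = 0.13/0.0638 = 2.04.

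| Events per 100 | t-test | Mann-Whitney | Uncorrected chi-square | Fisher, two-sided |
|---|---|---|---|---|
| 35 vs 22 | 0.042 | 0.042 | 0.042 | 0.060 |
| 40 vs 20 | 0.0019 | 0.0021 | 0.0020 | 0.0032 |

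On 0/1 data the two named tests are in effect an uncorrected chi-square test. Their type I error, enumerated for 50 and 100 per group with event rates of 10% to 30%, is 0.048 to 0.051. So the error rate is sound, but the result can fall on the other side of 0.05 from Fisher's test. Two-sided p-values are used so that like is compared with like; the plan sizes the trial two-sided and names a one-sided primary test. With equal groups the one-sided Fisher value in the first row is half of 0.0596, or 0.030.

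**3. McNemar's test against the data described.**

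| Test requires | Plan provides |
|---|---|
| Binary result | Questionnaire results, treated as scores in the preceding sentence |
| Two time points | Three: preoperative, 1 month, 9 months |
| Gives a within-patient change | Trial question is high versus low ligation |

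The named analysis cannot be run on the scores as they stand.

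**4. What baseline adjustment would add to the score comparisons.** Assumptions: a normal score, with 40% and 20% of patients beyond some cut. The shift is then d = z(0.40) − z(0.20) = −0.253 + 0.842 = 0.588 SD. With n per arm and correlation ρ between baseline and follow-up,

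power = Φ( d / √(2(1 − ρ²)/n) − 1.96 ).

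| n per arm | No baseline (ρ = 0) | ANCOVA, ρ = 0.5 |
|---|---|---|
| 100 | Φ(4.16 − 1.96) = 98.6% | Φ(4.80 − 1.96) = 99.8% |
| 60 (assumed) | Φ(3.22 − 1.96) = 90% | Φ(3.72 − 1.96) = 96% |
| 40 (assumed) | Φ(2.63 − 1.96) = 75% | Φ(3.04 − 1.96) = 86% |

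At 100 per arm, ρ = 0.3 gives 99.2% and ρ = 0.7 more than 99.9%. The split by sex is not in the document; 60 and 40 per arm illustrate the male-only and female-only questionnaires.

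**The case against.** The best defence is that this is loose wording in a condensed article, touching only supportive analyses. Much of that stands. A cut-off for each questionnaire, or a rule for choosing between the Mann-Whitney and t-tests, may well sit in an analysis plan that is not shown, and their absence is no fault here. Two-sample tests on scores in a randomised trial are valid without covariates, so the baseline point concerns efficiency only. What the defence does not remove is that the article positively assigns tests to data they do not fit.

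Some stronger readings are tempting, and the document does not support them.

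- A reader might infer that the by-sex analysis is invalid. Its type I error is near nominal, so it is mis-specified rather than invalid.
- A reader might infer that within-arm testing takes the place of the comparison of arms. It does not: Fisher's test and, on the natural reading, the two-sample tests on questionnaires compare high with low ligation. McNemar's test is additional, and the Discussion gives the effect of the operation itself on function as one purpose of testing before and after.
- A reader might fear a conclusion drawn from change in one arm and not in the other. Nothing says McNemar's test will be run by arm or used in that way.
- A reader might set the 84.45% power against the 98.6% for scores. The first belongs to the primary incidence endpoint, and the plan already compares questionnaire scores as scores, so that gap is not a loss the plan incurs.
- A reader might say that baseline is ignored altogether. The primary endpoint is defined against it, and a test of change over time would naturally include it.

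**Conclusion.** The point holds for the supportive functional analyses only. The tests named for incidences by sex are the wrong tools for proportions: they do little harm to the error rate, but can disagree with the method used for the same endpoint overall. McNemar's test does not fit scores at three times and would not compare the arms in any case. The between-arm score tests are valid but, as worded, forgo baseline information.

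The size is modest. Under the assumptions above, adjustment gains about 1 percentage point of power at 100 per arm, 6 at 60 and 11 at 40. These figures rest on normal scores, a 0.59 SD shift derived from incidences the document does not state, an assumed correlation and an assumed split by sex. The primary Fisher test and the sample size of 212 do not change. This should be fixed, but it does not threaten the main result.

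**What to change.** Reword the Statistical analysis section in three places.

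1. **Incidence by sex.** Compare arms by Fisher's exact test within each sex, or by logistic regression with arm, sex and arm-by-sex interaction. Drop the Mann-Whitney and t-tests for incidences.
2. **Questionnaire scores, uroflowmetry and post-void volume.** Compare arms on the 9-month value by ANCOVA with the baseline value as covariate, or use a repeated-measures model over 1 and 9 months. Use a rank-based version if residuals are clearly skewed.
3. **McNemar's test.** Restrict it to binary dysfunction status between two named time points, as description, with no conclusion about the arms drawn from it.

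The cost is wording alone. The preoperative, 1-month and 9-month assessments are already planned, no patient or visit is added, and Trial status says recruitment had not yet opened.

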## Background

Colorectal cancer incidence and mortality rates vary around the world. Globally, colorectal cancer is the third most commonly diagnosed cancer in men and the second in women [1]. Surgical treatment of rectal cancer has changed radically in recent years. The introduction of total mesorectal excision [2], neo-adjuvant therapy protocols [3], and the laparoscopic approach [4] has made rectal cancer treatment a multidisciplinary management.

While laparoscopic resection of colon cancer has slowly gained acceptance worldwide, the role of laparoscopy in the treatment of rectal cancer is still controversial [4,5]. The laparoscopic treatment of rectal cancer raises specific issues related to its anatomical location: difficult exposure in a narrow pelvis, challenging nerve-sparing techniques, low intestinal transection, and total mesorectal excision [6,7]. Ligation of the inferior mesenteric artery at the origin and mobilization of the splenic flexure are not routinely done worldwide [8-11]. The need for well-designed studies to compare the different vascular approaches in rectal surgery has been clearly expressed [12-14].

The level of arterial ligation can affect genito-urinary function (injury to the superior hypogastric plexus), the extent (and yield) of lymphadenectomy, and distal colonic arterial perfusion (especially in older people, where distal colonic arterial perfusion could be deficient due to degenerative disease), and causesympathetic nerve injures [15-19]. Moreover, colonic stump blood supply and anastomosis tension are the main factors in developing leaks in rectal surgery [20-26] and are dependent on the level of ligation.

The aim of this study is to compare the incidence of genito-urinary dysfunction and, secondarily, the incidence of anastomotic leakage and the oncological outcomes in laparoscopic anterior rectal resection with total mesorectal excision with high or low ligation of the inferior mesenteric artery in a controlled randomized trial.

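### The by-sex analysis of dysfunction does not state its contrast, and neither contrast it could mean shows whether the ligation effect differs between men and women

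*Protocol article*

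**What the plan says.** The Statistical analysis section gives the primary endpoint a Fisher's "exact test (one-sided") comparison. For "The different incidences of genitor-urinary dysfunction according to sex" it then names two other methods, a rank test (Mann–Whitney) and a t-test, and uses the same pair for the questionnaire scores. The sentence does not mention ligation arm, interaction or effect modification.

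The rest of the article frames the trial as one overall comparison. The Background states: "The aim of this study is to compare the incidence of genito-urinary dysfunction and, secondarily, the incidence of anastomotic leakage". The endpoint section states: "The primary end-point measure is the incidence of post-operative genito-urinary dysfunction compared with a preoperative base-line assessment in both groups". Neither names a sex-by-ligation question. The sample size likewise rests on one overall comparison: "A two tail Fischer exact test applied to two cohorts of 100 patients each".

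The preoperative and post-operative evaluation sections list an erectile function index and a female sexual function index. They also list a prostatic symptom score, an incontinence questionnaire, uroflowmetry and post-void bladder volume.

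**The concern.** Sex is the only subgroup the analysis section names, and the tests named for it are two-group tests. As a test, the sentence can be read in two ways.

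- **Men against women, arms pooled.** Sex is not randomised, and the sexual-function part of the assessment uses a different questionnaire in each sex. A difference could reflect underlying risk or the instrument, and it says nothing about ligation.
- **High against low ligation, tested separately in each sex.** This does concern ligation. However, each test uses only part of a sample sized for the overall effect, and two separate p-values do not compare the effects with each other.

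The interpretability of the one named subgroup analysis is at stake. The primary comparison is not affected.

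**Working it through.** **Inputs from the article.** 100 patients per arm, a 20-point difference, α = 0.05, 84.45% power with a two-tailed Fisher test (Sample size calculation); a one-sided Fisher test for the primary analysis (Statistical analysis).

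**Assumptions.** The base rates are not stated and are recovered in step 1. The sex mix is not stated; 50% to 70% men is used, the same in both arms.

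**Step 1. Reproduce the stated power.** Exact enumeration of the two-sided Fisher test, 100 per arm, 40% against 20%, gives 0.8445, which matches the article. The other 20-point pairs tried (25% v 5% up to 60% v 40%, in 5-point steps) do not match; they run from 78.7% to 98.1%. So 40% against 20% is used below.

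**Step 2. Arms compared within each sex, same true effect in both.** Let a and b be the exact Fisher power in men and in women. The two sexes are independent, so

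P(exactly one significant) = a(1 − b) + b(1 − a), and P(both significant) = ab.

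At 60% men (60 men and 40 women per arm), two-sided: a = 0.600, b = 0.408. Then 0.600 × 0.592 + 0.408 × 0.400 = 0.355 + 0.163 = 0.518.

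| Men | Two-sided a, b | Exactly one | Both | One-sided a, b | Exactly one |
|---|---|---|---|---|---|
| 50% | 0.515, 0.515 | 50.0% | 27% | 0.636, 0.636 | 46% |
| 60% | 0.600, 0.408 | 51.8% | 24% | 0.714, 0.538 | 48% |
| 65% | 0.641, 0.357 | 54.0% | 23% | 0.758, 0.473 | 51% |
| 70% | 0.683, 0.298 | 57.4% | 20% | 0.784, 0.417 | 55% |

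Fisher's test is not the test named for this analysis. A two-sided normal test, which closely approximates a t-test or Mann–Whitney test on 0/1 data, gives 48%, 50% and 52% at 50%, 60% and 65% men. The result does not depend on the test.

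**Step 3. Men against women, arms pooled (60% men, 200,000 simulated trials each).**

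- Ligation effect in men only, equal average risk (men 40%/20%, women 30%/30%): rejects in 4.8%. The effect modification is missed.
- Same 20-point effect in both sexes, different risk (men 50%/30%, women 30%/10%): rejects in 87%. This correctly detects a risk difference between the sexes but is not evidence on ligation.
- Same risk and same effect in both sexes: rejects in 4.6%.

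**Step 4. A direct arm-by-sex interaction test.** With 40% v 20% in both sexes, simulation gives a rejection rate of 4.2% to 4.6% on the log-odds scale over 50% to 70% men, and 5.4% on the risk-difference scale at 60% men.

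Its precision on the log-odds scale at 60/40 is

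SE = √[1/(60×0.24) + 1/(60×0.16) + 1/(40×0.24) + 1/(40×0.16)] = √(0.069 + 0.104 + 0.104 + 0.156) = √0.434 = 0.66.

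Its power, on the risk-difference scale, for 20 points in men (40% v 20%) and none in women (40% v 40%):

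SE = √[(0.24 + 0.16)/60 + (0.24 + 0.24)/40] = √0.01867 = 0.137; 0.20/0.137 − 1.96 ≈ −0.50, so power is about 31%. Over the mixes (50% to 65% men) and base rates tried it is 28% to 39%.

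**The case against.** The strongest reply is that the protocol never asks whether the ligation effect differs by sex. The aim, the endpoints and the expected result in the Discussion are all overall comparisons. An interaction model for a secondary breakdown is ordinary analysis-plan detail, and the full plan is not shown. Because sexual function needs different questionnaires in men and women, showing results by sex may be no more than description.

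Much of this stands. No effect-modification aim is stated, so none should be attributed to the sponsor. A reader might infer that the trial, followed as written, would often report an effect confined to one sex. The article does not support that. It gives no rule for claiming a sex-specific effect, and the misleading pattern needs three things together: the within-sex reading, a real overall effect, and an inference drawn from one significant and one non-significant p-value.

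A reader might also infer that the instruments alone would create a gap between men and women of some given size. The article offers no figure for that and does not say how the dysfunction event is composed. The incontinence questionnaire, uroflowmetry and post-void volume carry no sex restriction, so any link between sex and instrument is partial.

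What does not stand is that the matter is simply left to an unseen plan. The article does state a by-sex evaluation and names two-group tests for it. Whichever contrast is meant, that analysis cannot address a difference in ligation effect. The sample size detail does not help either, since it covers only the overall comparison.

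**Conclusion.** The point holds in a limited form. The by-sex analysis is ambiguous about its contrast, and under either reading it gives no comparison of the ligation effect between men and women. If arms are tested within each sex, a pattern of significance in one sex only is expected in about half of trials with identical true effects: 50% to 57% two-sided and 46% to 55% one-sided. This rests on 40% v 20%, recovered from the stated power, and on an assumed 50% to 70% men. It is a risk of misreading, and it arises when there is a real overall effect, which the Discussion expects. If men are compared with women, a significant result may be a true difference in risk but is not evidence on ligation. The weight is moderate to low: a cheap improvement to a secondary analysis, with the primary comparison and the sample size untouched.

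**What to change.** Replace the by-sex clause with a sentence stating that:

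- the analysis compares high with low ligation;
- the difference in dysfunction incidence is reported with a 95% CI in each sex;
- an arm-by-sex interaction is tested, for example in a logistic model with arm, sex and their product;
- any claim of a sex-specific effect rests on the interaction alone and is labelled exploratory.

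A men-against-women comparison may be kept as description, but not as evidence about ligation.

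The cost is one sentence of wording and no new data, and the article says recruitment has not opened. The downside is low interaction power (log-odds SE about 0.66 at 60/40; about 31% power for 20 points in one sex and none in the other), so a non-significant interaction must not be read as showing equal effects.
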